### Recruitment of patient participants

A software application, MedeMine CVD, has been installed on the dispensing computer of participating pharmacies. MedeMine CVD extracts data from the market leading pharmacy dispensing software system in Australia (FRED Dispense^®^) and identifies patients who are using or have used antihypertensive medicines in the previous six months. The purpose of MedeMine CVD is to:

1. preferentially identify patients who last had their antihypertensive medications dispensed more than 59 days previously and those with suboptimal refill adherence;

2. generate personalised "Expression of Interest" (EOI) forms to mail to potential patient participants. Once the completed EOI has been received by the pharmacist and eligibility is confirmed, the information is recorded in MedeMine CVD;

3. generate the participant explanatory statement and consent form, as well as a letter and fax-back form to be sent to the participant's GP to confirm diagnosis of primary hypertension and advise of the participant's target BP;

4. manage participant appointments by pharmacists;

5. create a unique identification number for each participant, which is printed on all study documents (e.g. data collection forms and letters); and

6. send SMS reminders or prompt the pharmacist to telephone or send mail reminders, to participants who have requested this part of the service, when their supplies are dwindling.

An invitation letter (EOI) with a short questionnaire (seeking information about the patient's BP, interest in participation, nominated GP, including contact details and consent to contact the GP, and patient telephone contact details) and a reply-paid envelope were sent to potential participants. Patients were asked to return the completed questionnaire to the pharmacy and indicate their interest in participating. Once the EOI is received, the pharmacist will contact the patient to further assess their eligibility and arrange a mutually convenient time to visit the pharmacy to enrol in the study. If eligibility is confirmed, the consent form would then be signed. The pharmacist will also contact the patient's GP. At no point are patients' identities made known to the researchers.

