### Primary outcome measures

The primary outcomes of the HAPPY trial are changes in patient adherence and persistence at the end of six months. These will be measured subjectively using the self-reported Morisky scale [16] and the Tool for Adherence Behaviour Screening (TABS) [17] and objectively using the medication refill data (e.g. MedsIndex score [18]). The Morisky scale assesses both intentional and unintentional nonadherence and comprises four items. Responses for each item are scored 0 for 'yes' and 1 for 'no' (except for the item 'are you always careful in taking medicines?' where the score was reversed) and added together. A total score of zero represents good adherence and a score of one or more represents suboptimal adherence. The TABS is another self-reported adherence measure, which was originally developed in Australian patients using chronic medicines. It has two subscales - 'adherence' and 'nonadherence' - each comprising four items to be answered on a 5-point Likert-type scale ('never' - 1 to 'always' - 5). The total score for 'nonadherence' will be subtracted from that of 'adherence'; a differential of ≥15 will be regarded as good adherence and ≤14 will be regarded as suboptimal adherence. The TABS measures both intentional and unintentional deviations from recommended management and has been shown to have greater incremental validity than other self-reported adherence measures [17]. The MedsIndex gives each patient a score out of 100 for each of their long-term medications, which is calculated based on their refill history. Any score less than 100 suggests suboptimal adherence.

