### Pharmacist Care Group (PCG)

The PCG participants receive a package of interventions from the pharmacist for enhancing their antihypertensive medication adherence, which includes:

• a home BP monitor (Omron^®^T9IT) with the capacity to store and download BP readings to be used for discussion at three- and six-month follow-ups;

• training by the pharmacist on self-monitoring of BP;

• motivational interviewing and education by the pharmacist to help patients improve their medication adherence and achieve target BP;

• pharmacist-initiated home medicines review (HMR), dose administration aid (DAA) and/or patient medication profile (PMP), where necessary;

• medication use review (MUR) to identify and resolve possible medication-related hypertension (e.g. due to non-steroidal anti-inflammatory drugs, cold preparations, complementary medicines, etc.);

• referral to a GP when needed (e.g. very high blood pressure); and

• refill reminders (by either SMS, telephone or mail) from their pharmacist at a chosen number of days before their antihypertensive medication dispensing is due.

HMRs http://www.medicareaustralia.gov.au/provider/pbs/fourth-agreement/hmr.jsp are designed to assist consumers living at home to maximise the benefits of their medication regimen and prevent medication-related problems. The review involves the consumer's general practitioner (GP) and preferred community pharmacy, and in some cases other relevant members of the healthcare team. The GP refers the consumer to the community pharmacy and an accredited pharmacist visits the consumer at home, reviews their medication regimen, and provides the GP with a report. The GP and consumer then agree on a medication management plan.

A DAA http://www.health.gov.au/internet/main/publishing.nsf/Content/ppsac-qa-daa is a device developed to assist patients in better managing their medicines by arranging their medicines into individual doses according to the prescribed dose schedule throughout the day. The aim of the DAA Program is to reduce medication-related hospitalisation and adverse events through improving medication management and adherence for people in the community.

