### Inclusion criteria

• using or having used in the last six months at least one antihypertensive medication belonging to the four most common classes of antihypertensives in Australia - angiotensin converting enzyme inhibitors angiotensin-II receptor antagonists, calcium channel blockers, beta blockers -  http://www.aihw.gov.au/publications/cvd/mfchatua/mfchatua.pdf or fixed combinations of antihypertensive medications belonging to the above classes with other antihypertensives (e.g. diuretics);

• a diagnosis of primary hypertension;

• 18 years and above; and

• available for follow-up for at least six months from baseline.

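### The objective adherence measure appears to rest on one pharmacy's dispensing record, so a greater shift of refills to that pharmacy in the PCG could pass for better adherence

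*Protocol article*

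**What the plan says.** **Measure.** Under *Primary outcome measures*, adherence and persistence are assessed by two self-reports (Morisky, TABS) and by refill data. Only the refill data are called objective. MedsIndex is the example given: a score out of 100 for each medicine, "which is calculated based on their refill history". "Any score less than 100 suggests suboptimal adherence".

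**Source of the record.** Under *Recruitment of patient participants*, the MedeMine CVD software "has been installed on the dispensing computer of participating pharmacies" and reads that pharmacy's FRED Dispense data. Under *Phase I*, pharmacists are trained to calculate MedsIndex. *Ethics* describes the hidden-control refill data as what the pharmacist can see in the dispensing program. No claims database or linked source is named.

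**Who is invited.** The software is to "preferentially identify patients who last had their antihypertensive medications dispensed more than 59 days previously and those with suboptimal refill adherence". The medication criterion is "using or having used in the last six months at least one antihypertensive medication" from the listed classes. Nothing in *Inclusion criteria* or *Exclusion criteria* concerns where the medicine is obtained.

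**What differs by arm.** The PCG package includes "refill reminders (by either SMS, telephone or mail) from their pharmacist at a chosen number of days before their antihypertensive medication dispensing is due", pharmacist-initiated HMR, DAA or PMP where necessary, and a three-month visit. The UCG continues with routine care and attends at baseline and six months.

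**Analysis.** *Data analysis* compares changes in total MedsIndex score between PCG and UCG.

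**The concern.** In a single pharmacy's record, a patient who has stopped treatment and a patient who fills at another pharmacy look alike: both show a gap. If the second patient later moves all refills to the study pharmacy, the recorded score rises although not one more dose has been taken.

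Randomisation does not remove this if the intervention itself makes the record more complete. Reminders from the study pharmacist, packing of doses and an extra visit all give PCG patients more reason to refill there. The error would then run in one direction, toward the intervention, and it would sit in the only primary measure that does not depend on what patients say to their own pharmacist.

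**Working it through.** **1. The plan's own figure.** For 50% versus 65% adherent, 80% power and two-sided 0.05, the two-proportion formula with continuity correction gives 183 per group, against the stated 182. Without the correction it gives 170. The stated figure reproduces, and 15 percentage points is the yardstick used below.

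**2. The chain, link by link.**

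- Refill data are the only objective primary measure: stated.
- The refill history covers the study pharmacy only: inferred from where the software sits and from the dispensing-program wording. It is not stated outright, but nothing points to another source.
- Patients who fill elsewhere are eligible: follows from the listed criteria.
- Recruitment favours gaps in the record: stated, and it applies in both arms.
- PCG patients have the stronger reason to move refills: follows from the components given only to the PCG during the six months.

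**3. Size on the percent-adherent scale.** The documents give neither input, so both are assumptions:

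- *m* = share of enrolled patients whose recorded shortfall is due only to filling elsewhere, and who would reach the cut-off of 100 if every refill were recorded (5% to 30%);
- *c* = share of those patients who move refills to the study pharmacy in the PCG, minus the corresponding share in the UCG (10% to 75%).

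False difference = *m* × *c*. The brackets give the probability that a two-sided 0.05 test rejects when medicine taking has not changed, with 182 per group, 50% in the UCG, no continuity correction and clustering ignored.

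| *m* | *c* = 10% | *c* = 25% | *c* = 50% | *c* = 75% |
|---|---|---|---|---|
| 5% | 0.5 (0.051) | 1.25 (0.057) | 2.5 (0.076) | 3.75 (0.110) |
| 10% | 1.0 (0.054) | 2.5 (0.076) | 5.0 (0.159) | 7.5 (0.300) |
| 20% | 2.0 (0.067) | 5.0 (0.159) | 10.0 (0.483) | 15.0 (0.828) |
| 30% | 3.0 (0.088) | 7.5 (0.300) | 15.0 (0.828) | 22.5 (0.994) |

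Relative to the planned difference, this runs from 0.5/15 = 3% to 22.5/15 = 150%.

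**4. Size on the score scale, which the planned comparison uses.** Take a patient who truly takes 90% of doses:

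- half of supplies from the study pharmacy: recorded 90 × 0.5 = 45; after moving all refills, 90; gain 45;
- 70% of supplies from the study pharmacy: recorded 90 × 0.7 = 63; after moving all refills, 90; gain 27.

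Such a patient stays below 100 and so adds nothing to percent adherent, but does raise the mean change. The false difference in mean change is (share filling partly elsewhere) × *c* × gain. Over the same assumed ranges it runs from 0.05 × 0.10 × 27 = 0.135 to 0.30 × 0.75 × 45 = 10.125 MedsIndex points. At 10%, 50% and a gain of 45 it is 2.25. The article gives no standard deviation for MedsIndex change, so these values cannot be turned into rejection probabilities.

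**The case against.** - **Silence in a condensed article.** Form items and MedsIndex scoring rules may be in the full protocol, and the baseline visit does gather information on the patient's medications. This stands: the absence of a supply question from the article is not itself an error. The point rests on what the article does state, namely the local record, the open eligibility and the unequal pull between arms.
- **The UCG has some pull too.** Its patients are invited by the study pharmacy, attend there at baseline and six months, and are promised the package afterwards. This stands: only the excess in the PCG matters, which is why *c* is defined as a difference.
- **The PCG pull is partial.** Reminders go to those who ask for them, DAA, HMR and PMP are used where necessary, and there is one extra visit. This stands, and it favours the lower values of *c*.
- **The recruitment rule.** A reader might infer that favouring patients with gaps creates the bias. It does not: the rule applies in both arms and alone would mainly produce regression to the mean in both. It can enlarge the susceptible group, though patients who fill elsewhere must also respond to an invitation from a pharmacy they may seldom use.
- **Other outcomes are untouched.** Morisky, TABS and blood pressure do not depend on where refills are recorded, so a rise in MedsIndex alone would look discordant. This is a partial safeguard. The two scales are self-reports, administered by the pharmacist at least at the PCG three-month visit, so they are weak substitutes for an objective check.
- **The hidden control group** does not settle the matter. It is compared only with the UCG and uses the same kind of record.

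**Conclusion.** The point holds as a potential bias toward the intervention in the objective primary measure. Part of any PCG-UCG difference in MedsIndex change could reflect where refills are recorded and not medicine taking.

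The size is unknown. Under the assumed ranges the false difference in percent adherent runs from 0.5 points, which is negligible, to 22.5 points, which exceeds the planned 15. Those figures apply only to patients who would reach 100 once all refills were counted. The verdict also assumes that the refill history covers one pharmacy, which is inferred.

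A reader might go further and conclude that a shift in pharmacy loyalty will yield a false positive trial, or that a gain of a particular size is to be expected. The documents do not support either. They give no rate of multiple-pharmacy use and no rate of return by arm, the UCG has some pull of its own, and the other primary measures would not move. The change is still worth making, because the direction of the bias is known and a simple question would show whether it matters.

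**What to change.** 1. At the baseline and six-month visits, in both arms, ask whether any antihypertensive was obtained from another source in the past six months, and how much. In the PCG, ask at baseline before the intervention is delivered.
2. Report the PCG-UCG comparison of MedsIndex change with and without those outside supplies counted.
3. As a sensitivity analysis, repeat the comparison in patients who at baseline reported using only the study pharmacy. Do not define this subset by use of only the study pharmacy in both periods: the second period follows the start of the intervention, which may itself change where patients refill, and conditioning on it would introduce selection bias.
4. State in the protocol whether the refill history covers the study pharmacy only.

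**Cost.** One short question at two visits already planned, and two extra analyses. Outside supply would be self-reported to pharmacists who know the allocation, so the corrected score is itself imperfect, and the restricted comparison has fewer patients.

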### Inclusion criteria

• using or having used in the last six months at least one antihypertensive medication belonging to the four most common classes of antihypertensives in Australia - angiotensin converting enzyme inhibitors angiotensin-II receptor antagonists, calcium channel blockers, beta blockers -  http://www.aihw.gov.au/publications/cvd/mfchatua/mfchatua.pdf or fixed combinations of antihypertensive medications belonging to the above classes with other antihypertensives (e.g. diuretics);

• a diagnosis of primary hypertension;

• 18 years and above; and

• available for follow-up for at least six months from baseline.

### Exclusion criteria

• participation in other adherence promotion programs;

• having had a pharmacist-conducted HMR service in the last 12 months;

• unable to communicate in English; and

• does not self-administer antihypertensive medicines.

Each pharmacist was asked to recruit 7-10 patients from their pharmacy.

### Data collection

### Baseline visit

During the baseline visit to the pharmacy, the pharmacist will measure the patient's BP using a digital BP monitor (average of two readings as per WHO MONICA [23] and EHRM [24] protocols - if these differ by more than 5 mmHg, a third reading will be taken and the average of the two closest readings will be recorded). Each pharmacy has been provided with a BP monitor. The MedsIndex score will be calculated for each antihypertensive medicine the patient uses. Adherence will be measured using self-report tools - the Morisky scale and the TABS. The Beliefs and Behaviour Questionnaire [17] will be used to assess patient experiences, attitudes and beliefs regarding their health and treatment and the 8-item short Assessment of Quality of Life (AQoL) [25] will be used to measure health-related quality of life. The pharmacist will also collect information on the patient's medications and their understanding of and ability to use these medications. The PCG will also receive the intervention described earlier.

### Three-month visit

#### Pharmacist Care Group (PCG) Only

During the patient's visit to the pharmacy at three months, the pharmacist will administer the Morisky scale and TABS. The pharmacist will also:

• download the patient's home BP measurements for review and discussion with the patient;

• measure patient's BP (as described above);

• document any adherence issues and actions taken; and

• refer patient to their GP, if needed (e.g. persistent uncontrolled BP even after improvement in adherence).

### Six-month visit (Final project visit)

Measures performed at baseline will be repeated for both UCG and PCG patients at their six-month visit to the pharmacy.

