### Sample size

Australian, European and North American studies have estimated that around 50% of patients initiating an antihypertensive medication discontinue their medication (become nonpersistent) within twelve months [22]. To demonstrate a 15% difference in adherence between the control and intervention groups at six months (e.g. 50% in the UCG versus 65% in the PCG) with 80% power and a two-sided p-value of 0.05, 182 patients are required per study group. To allow for potential drop-outs (approximately 25% over six months) 225 patients need to be recruited per group; i.e. a total of 450 patients at baseline.

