### Data analysis

Participant characteristics in the UCG and PCG will be compared at baseline. Paired t-tests and/or Wilcoxon Signed Rank test will be used to compare changes in total scores on the Morisky scale, TABS and MedsIndex between the PCG and the UCG at baseline and six months. MedsIndex scores will be compared using paired t-tests and/or Wilcoxon Signed Rank test in the UCG and the HCG at six months.

Baseline data will be used to identify factors associated with suboptimal adherence in the whole study population. Significant factors in univariate analysis (chi-square, Mann-Whitney U test and Student's t-test) will be further tested in multivariate analysis (linear regression) to identify independent predictors of nonadherence/nonpersistence in the study population. To adjust for cluster randomisation, a pharmacy variable will also be included in the multivariate models.

An economic evaluation will also be carried out and will be reported elsewhere.

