### Ethics

This project has been approved by the Human Research Ethics Committees of Monash University, Curtin University and The University of Melbourne, and the Human Research Ethics Network of Tasmania. All pharmacists and patient participants (in the UCG and PCG) provided written informed consent at the time of enrolment.

Approval to access dispensing data for the HCG was given on the basis that pharmacists have routine access to this data about their patients via the dispensing program and would use it in normal practice to routinely check their patient's history for actual or potential medication-related problems. The researchers will have access only to deidentified patient data.

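### The refill-based primary measure is scheduled at the six-month visit for both randomised arms, although dispensing records could supply it for patients who do not attend

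*Protocol article*

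**What the plan says.** The Primary outcome measures section names changes in adherence and persistence at the end of six months as primary. They are measured by two self-report scales and by refill data, for which MedsIndex is the example. MedsIndex is a score out of 100 for each long-term medicine, "which is calculated based on their refill history".

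The Baseline visit section lists it among the measures made at that visit: "The MedsIndex score will be calculated for each antihypertensive medicine the patient uses". The Six-month visit section then says: "Measures performed at baseline will be repeated for both UCG and PCG patients at their six-month visit to the pharmacy". No other collection route is described for the PCG or UCG.

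Three other sections bear on the point:

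- **Recruitment of patient participants.** The trial software is installed on each pharmacy's dispensing computer: "MedeMine CVD extracts data from the market leading pharmacy dispensing software system in Australia".
- **Data analysis and Ethics.** The HCG has no study visit, yet "MedsIndex scores will be compared using paired t-tests and/or Wilcoxon Signed Rank test in the UCG and the HCG at six months". The source is the pharmacy record: "Approval to access dispensing data for the HCG was given on the basis that pharmacists have routine access to this data about their patients".
- **Sample size.** "To allow for potential drop-outs (approximately 25% over six months) 225 patients need to be recruited per group".

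**The concern.** A refill score needs no answer or attendance from the patient, because it is computed from records that the pharmacy already holds. Tying it to a visit exposes the one objective primary measure to the same losses as the questionnaires and blood pressure.

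Those losses may not be random. Persistence is a primary outcome, and the final visit takes place at the pharmacy where refills are collected, so a patient who has stopped refilling may also be less likely to come. The software preferentially identifies patients with long gaps since dispensing or poor refill adherence. Reasons to attend also differ by arm. The PCG has refill reminders, home blood-pressure review and a three-month visit. The UCG is offered the intervention package after final measurement, which the article expects to help retention.

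At stake are the precision of the refill comparison, possible bias in the PCG-UCG difference, and a like-for-like Hawthorne check between UCG and HCG.

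**Working it through.** **Inputs from the Sample size section:** 50% v 65%, two-sided 0.05, 80% power, 182 per group, about 25% drop-out, 225 recruited per group. The abstract gives 56 pharmacies. An equal split of 28 per arm is an assumption.

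**1. The plan's own figure.** With a pooled null variance,

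n = [1.960·√(2·0.575·0.425) + 0.842·√(0.50·0.50 + 0.65·0.35)]² / 0.15² = 169.3, so 170.

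With continuity correction, (169.3/4)·[1 + √(1 + 4/(169.3·0.15))]² = 182.4. This reproduces the stated 182 (183 if rounded up).

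**2. Patients affected.** 0.25 × 225 = 56.25, so about 56 per group would have no visit-based value and about 169 would have one. This is an upper figure, because it takes every drop-out to miss the visit and every record to be recoverable.

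**3. Precision.** √(169/225) = 0.867. Using all 225 makes the standard error about 13% smaller. Put the other way, 225/169 has square root 1.154, so attenders alone give one about 15% larger.

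Power for 50% v 65% (normal approximation, no continuity correction) is shown below. The design effect is 1 + (m − 1)·ICC, with m = 169/28 = 6.04 or 225/28 = 8.04. The article gives no ICC, so these values are assumptions.

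| Assumed ICC | Effective n, 169 | Power | Effective n, 225 | Power | SE ratio |
|---|---|---|---|---|---|
| 0 | 169.0 | 80% | 225.0 | 90% | 0.87 |
| 0.01 | 160.9 | 78% | 210.2 | 88% | 0.87 |
| 0.05 | 135.0 | 70% | 166.4 | 79% | 0.90 |

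The gain shrinks as clustering grows, to about 10% in standard error at an ICC of 0.05.

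**4. Bias, under assumptions.** Let P be true adherence in an arm, a the proportion not attending and q adherence among non-attenders. Attenders then show (P − a·q)/(1 − a). The article gives neither q nor arm-specific values of a.

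No true effect, P = 0.50 in both arms and the same q in both:

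| Non-attendance by arm | q | Attenders | False difference |
|---|---|---|---|
| 20% v 30% | 0.25 | 56.2% v 60.7% | 4.5 points |
| 20% v 30% | 0.20 | 57.5% v 62.9% | 5.4 points |
| 20% v 30% | 0.10 | 60.0% v 67.1% | 7.1 points |
| 20% v 35% | 0.20 | 57.5% v 66.2% | 8.7 points |
| 25% v 25% | any | equal | 0 |
| any | 0.50 | 50% v 50% | 0 |

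The false difference favours whichever arm loses more patients. The planned difference is 15 points.

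Equal attrition is not always harmless when there is a true effect. With P = 0.50 and 0.65, a = 0.25 and q = 0.25 in both arms, attenders show 58.3% v 78.3%, a difference of 20 points instead of 15. If non-attenders are as adherent as the rest of their own arm, the difference stays at 15 and only precision is lost.

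**The case against.** The strongest reply is that the article says when measures are repeated, not what happens to patients who do not attend. The Primary outcome measures section refers to the end of six months, and the Data analysis section to baseline and six months. Neither restricts the refill analysis to attenders. A condensed article may leave this to the full protocol or analysis plan. The HCG arrangement shows that the team had the means to extract records without a visit, and does not show that it chose not to use them for non-attenders. This stands: a reader might infer that non-attenders are dropped from the result, but the text does not say so.

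Two further readings also go beyond the text. The Sample size section does not say that drop-outs are lost to every outcome; it makes one allowance on a single adherence proportion. Nor does any section give adherence among non-attenders, so it is not established that they are the patients who stopped treatment, or that adherence is overstated in both arms.

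Extraction has its own weakness. The software reads one pharmacy's records and no cross-pharmacy source is described, so a patient who now fills elsewhere would look non-persistent. Some missing data would become possible misclassification, in the same patients.

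The objection does not remove the point that the stated schedule links the measure to a visit. Nor can a later analysis plan repair this alone. Researchers never learn patients' identities, so pharmacists must be told to pull the record; an analysis plan can model a missing value but not collect it.

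**Conclusion.** The point holds as a fault in the stated collection schedule, and should be fixed. Followed as written, up to about 56 of 225 patients per group lack a six-month refill value that dispensing records could supply. The cost in precision is a standard error that could be about 13% smaller with all 225, or about 10% smaller with an assumed ICC of 0.05. These figures require usable records for every recruited patient, so they are upper limits. The UCG-HCG check would also set attenders beside a group with no attendance requirement.

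Bias in the PCG-UCG difference is a risk and not a finding. The range of about 4 to 9 points rests on assumed unequal attrition and assumed low adherence among non-attenders. It is zero under no effect with equal attrition and equal non-attender adherence, and zero whenever non-attenders are as adherent as the rest of their arm. Neither its direction nor its presence can be settled from the article, which is why this is not a must-fix.

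**What to change.** In the Six-month visit section, separate the refill outcome from attendance. State that pharmacists extract the dispensing history, and compute MedsIndex and persistence at baseline plus six months, for every enrolled PCG and UCG patient who has not withdrawn consent to data use, whether or not the patient attends, by the same method as for the HCG. Analyse the refill outcome in all of these patients. Keep the visit as the source for the Morisky scale, TABS, blood pressure and the other visit measures.

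Record known changes of pharmacy, state how they are handled, and add a sensitivity analysis restricted to attenders, so that the effect of misclassified switchers can be seen.

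The cost is small: one sentence in the schedule, a record pull with software already installed, and a check that consent covers dispensing data after a missed visit. No extra visits or patients are needed. One timing point needs attention. For patients enrolled in August 2009, baseline plus six months falls in February 2010, after the six-month collection window in the Study timeline and in the month set for analysis, so the extraction date must be reconciled with that timeline.
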